[15]. There is also growing evidence that internet-based interventions are cost effective
[16]. Family caregivers may favor internet interventions instead of meeting in a group or meeting with a professional face-to-face, due to lack of time or preferences concerning privacy. Caregivers may also be unwilling to visit a mental health care institute for themselves because in their view they are not the ones who need help. Given the growing internet sophistication of middle aged and older adults, it is expected that the number of potential users of internet interventions will grow substantially.

Until recently internet-based interventions were not developed for family caregivers of people with dementia. In November 2008, the innovative eMental Health intervention for family caregivers of people with dementia, called ‘Mastery over Dementia’, was launched in the Netherlands (for an English demo:
http://www.masteryoverdementia.com). In this paper the design of the RCT to evaluate the effectiveness and cost-effectiveness of ‘Mastery over Dementia’ for caregivers of people with dementia will be described. The specific research questions are:

1. Is ‘Mastery over Dementia’ superior compared to ‘care as usual’ in terms of a clinically significant reduction in depressive symptoms, symptoms of anxiety, role overload and caregiver perceived stress?

2. Are effects maintained up to six months after ending the internet intervention?

3. Which caregivers respond best to the intervention compared to others?

4. Is the internet intervention cost effective from a societal perspective compared to the comparison group?

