## Methods and design

To evaluate the effectiveness of ‘Mastery over Dementia’, we carry out a pragmatic randomized control trial (RCT). In the RCT there are two parallel groups. The experimental condition in which caregivers take part in the intervention (Mastery over Dementia) will be compared with a comparison condition in which caregivers receive a ‘minimal intervention’. The study protocol, information brochure and informed consent procedure were approved by the Medical Ethics Committee (METIGG, CCMO: NL27434.097.09).

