### Randomization

Randomization into two groups (experimental group and comparison group) takes place after assessment. Before randomization participants are stratified on the basis of two factors (sex: male/female and relationship: spouse/other). As a method for randomization block randomization with variable sizes is used. The allocation schedule is made with a computerized random number generator by an independent researcher and is unknown to the investigators of this study.

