##### Primary outcome measure: depressive symptoms

Depressive symptoms are measured with the Centre for Epidemiological Studies Depression scale (CES-D). The CES-D is a widely used self-report measure for the screening of depressive symptoms, and has also been used in research on caregiving. The Dutch version of the CES-D
[18] is used in this study. It consists of 20 items for which subjects rate the frequency of symptoms during the past week. Scores range from 0 (rarely or none of the time present [less than 1 day]) to 3 (most or all of the time present [5-7 days]). The total score range is 0–60. Items represent major components of depressive symptomatology such as depressed mood, feelings of guilt and worthlessness, feelings of helplessness and hopelessness, psychomotor retardation, loss of appetite, and sleep disturbance. A shortened version of the CES-D on internet (not used in this study) was found to be reliable in an adult population
[19].

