### Sample size

Symptoms of depression are the primary outcome measures and are used as starting point for the power calculations. A standardized effect size (Cohen's *d*) of 0.50 is considered a relevant treatment effect. Assuming an alpha of 0.05 and a statistical power (1-Beta) of 0.80 in a two-tailed test, we need 63 respondents in each of the conditions. Overall, we need 126 respondents to complete the study in total. Because we expect a minimum of 25 percent of caregivers to drop out during the data collection, we will recruit at least 175 caregivers. The numbers are calculated in Stata 7.0 (StataCorp 2001).

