### Statistical analysis

All analyses in the RCT-study will be conducted according to the intention to treat principle. Missing data on follow-up measurements will be imputed using regression imputation. To examine differences between the outcomes for experimental and comparison group, paired t-tests will be conducted and estimates of effect sizes will be calculated. By using multiple regression analyses, we can correct for possible confounders. With a ‘generalized estimated equations’ (GEE) analysis the research question regarding the maintenance of the effectiveness of the intervention will be answered. In addition, profiles of caregivers who respond best to the intervention will be described by means of a multiple regression analysis which also contains modifying variables (modifier analysis). All analyses will be conducted using SPSS for Windows, version 19.

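### Paired t-tests are named for the difference between two unmatched parallel arms; the plan should name a between-arm analysis of post-test CES-D as primary

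*Protocol article*

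**What the plan says.** Under Methods and design, the article describes the layout: "In the RCT there are two parallel groups". Under Randomization, individual caregivers are allocated within strata of sex and relationship: "As a method for randomization block randomization with variable sizes is used". Nothing there matches a caregiver in one arm to a caregiver in the other.

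The first research question, in Background, is comparative: "Is ‘Mastery over Dementia’ superior compared to ‘care as usual’ in terms of a clinically significant reduction in depressive symptoms". The primary outcome is depressive symptoms on the CES-D.

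Under Sample size, for d = 0.50, two-sided alpha 0.05 and power 0.80, the article says "we need 63 respondents in each of the conditions".

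The Statistical analysis section then names the test for the arm difference: "To examine differences between the outcomes for experimental and comparison group, paired t-tests will be conducted". It adds effect-size estimates and goes on: "By using multiple regression analyses, we can correct for possible confounders". GEE has a separate task: with it, "analysis the research question regarding the maintenance of the effectiveness of the intervention will be answered". A further multiple regression is reserved for the modifier analysis. Neither an independent-samples test nor an ANCOVA is named.

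**The concern.** The sentence joins a purpose (the difference between arms) to a test that cannot serve it. A paired t-test needs linked observations. In this design the links are the repeated measurements on one caregiver, so the test can show only whether an arm changed over time. Pairing unrelated caregivers across arms would be arbitrary.

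A change within an arm mixes any effect of the course with natural course and with whatever the minimal intervention also produces. Setting a significant change in one arm beside a non-significant change in the other is not a test of the randomised difference and does not hold the type I error at 5%. The primary efficacy conclusion is at stake, and the 80% power was not calculated for the test named.

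This is not a detail left to a fuller document. The article does name a method for the comparison, and that method does not fit the design.

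**Working it through.** **1. Reproduce the plan's sample size.** Inputs from Sample size: d = 0.50, two-sided alpha 0.05, power 0.80.

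- Independent two-sample formula: n per arm = 2(1.96 + 0.8416)² / 0.50² = 62.8, so 63. The stated figure reproduces.
- With the t distribution, 63 per arm gives 79.5% power, and 64 per arm are needed for 80%.

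**2. Compare with the test named.** If d = 0.50 were the standardised paired difference, n = (1.96 + 0.8416)² / 0.50² = 31.4, so 32 pairs, or 34 with the t distribution. The figure of 63 therefore comes from an independent-groups comparison.

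**3. See whether another planned analysis supplies the contrast.**

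- The first multiple regression is introduced for confounder correction. No arm term, form of outcome or primary status is stated.
- GEE is assigned to maintenance. The 9- and 12-month measurements that bear on this exist in the experimental arm only (Measures and measurement).
- The second regression is for effect modifiers.

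None of these is designated as the primary test of the arm difference.

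**4. Size of the possible error.** The following are assumptions and are not in the article: no true arm difference, the same improvement δ (in SD units) in both arms, pre-post correlation r, 63 per arm, and efficacy declared when the experimental arm's paired test is significant and the comparison arm's is not.

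- SD of change = √(2 − 2r).
- Noncentrality = δ√63 / √(2 − 2r), with 62 degrees of freedom. This gives p, the probability that one arm's paired test is significant.
- The arms are independent, so the pattern has probability p(1 − p), which can never exceed 25%.

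| r | δ | p | p(1 − p) |
|---|---|---|---|
| 0.5 | 0 | 5.0% | 4.8% |
| 0.5 | 0.1 | 12.2% | 10.7% |
| 0.5 | 0.2 | 34.6% | 22.6% |
| 0.5 | 0.3 | 65.0% | 22.8% |
| 0.5 | 0.4 | 87.8% | 10.7% |
| 0.5 | 0.5 | 97.4% | 2.5% |
| 0.7 | 0.2 | 52.3% | 24.9% |
| 0.7 | 0.3 | 85.7% | 12.3% |
| 0.7 | 0.4 | 98.1% | 1.9% |

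For example, with r = 0.5 and δ = 0.2 the SD of change is 1, the noncentrality is 0.2 × 7.937 = 1.587, p = 0.346, and p(1 − p) = 0.346 × 0.654 = 0.226.

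**5. Contrast with a valid test.** In simulation under the same null settings (δ from 0 to 0.5, r from 0.5 to 0.7), an independent-samples test on post-test scores or on change scores rejected in about 5% of trials throughout.

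**The case against.** The strongest reply is that this is a slip in a condensed article. The sentence states a between-group purpose, effect sizes are promised, and the sample size is the two-sample one. On this reading the authors meant an independent-samples test and wrote the wrong name. That may well be so, but the sentence as it stands still names an unsuitable test, and no other sentence names a suitable one.

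The second reply is that the regression in the next sentence may carry the comparison. With an arm term it would be a valid contrast. This stands as a limit on the consequence but does not repair the error, because the arm term is not stated and the analysis is not made primary.

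A reader might infer more than the article supports:

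- **That the primary question will be decided on within-arm change.** The article never says so, and the regression sentence leaves another route open.
- **That the false-positive rate is about 23%.** This needs a decision rule the article does not state, and settings (δ of 0.2 to 0.3 at r = 0.5) close to the 25% ceiling. Other settings give under 3%.
- **That regression to the mean must be large because the intake CES-D is also a screening score.** Table 1 does show the pre-treatment CES-D at intake only. However, the Recruitment section admits caregivers on any one of three criteria, and the CES-D one is a score above 4 on a 0–60 scale. Some regression to the mean is possible, but its size is not shown.

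**Conclusion.** The point holds in a limited form. The test named for the arm difference does not fit two unmatched parallel arms, does not answer the first research question, and is not the test behind the 80% power. This follows from the article's own text and arithmetic, without outside assumptions.

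The inflation of the type I error is conditional. It ranges from under 3% to about 25% across the settings examined, and only if efficacy is read from the pattern of significance in the two arms. A low figure at large δ is no reassurance, since the experimental arm's own paired test is then significant in more than 97% of trials with no true difference.

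Nor does the mismatch mean that the trial was sized wrongly. The figure of 63 per arm suits the comparison that should be made. Because the flaw concerns the primary comparison, the sentence should be corrected before analysis.

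**What to change.** Replace the paired t-tests with a between-arm comparison of CES-D at T=3 and state that it is the primary analysis. An independent-samples comparison would correct the error. ANCOVA or linear regression is preferable, with arm, intake CES-D and the two stratification factors (sex, relationship). Report the adjusted mean difference, its 95% confidence interval and a standardised effect.

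Use the same T=3 model for the secondary outcomes, with the baselines that Table 1 provides: intake for HADS-A, and T=1 for SPPIC and RMBPC. RMBPC is not measured at T=2, so a common model should not rely on that time point. Keep within-arm changes descriptive.

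The cost is a rewording of the analysis section, essentially one sentence. The sample size stays as it is, and no additional data are needed.

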#### Outcome measures in the RCT

For an overview of the instruments see Table
1.

**Table 1 T1:** Overview of instruments (measures)

	**Pre-test**			**Post-tests**		
	**Intake**	**T = 1**	**T = 2**	**T = 3**	**T = 4**	**T = 5**
Outcome measures in the RCT						
-* Depressive symptoms: CES-D*	X		X	X	X	X
- *Anxiety symptoms: HADS-A*	X		X	X	X	X
- *Role overload: SPPIC*		X	X	X	X	X
- *Caregiver perceived stress: RMBPC*		X		X	X	X
Confounders/Modifying variables						
- *Perceived control: Mastery Scale*		X		X	X	X
- *Sense of competence: SSCQ*		X		X	X	X
- *Behavioral problems: RMBPC*		X		X	X	X
- *Demographic variables*	X					
- *Diagnosis/Duration of symptoms*	X					
- *Functional status of person with dementia: IQCODE*	X					
Outcome measures in the CEA						
- *Quality of life: EQ-5D+C*		X		X	X	X
- *Health care utilization: TIC-P*		X		X	X	X
- *Time spent on caregiving*	X			X	X	X

*CES-D* Centre for Epidemiological Studies Depression scale.

*EQ-5D+C* EuroQol 5 Dimensions plus Cognition.

*HADS-A* Hospital Anxiety and Depression Scale, Anxiety subscale.

*IQCODE* Informant Questionnaire on Cognitive Decline in the Elderly.

*RMBPC* Revised Memory and Behavioral Problem Checklist.

*SPPIC* Self Perceived Pressure from Informal Care scale.

*SSCQ* Short Sense of Competence Questionnaire.

*TIC-P* iMTA Questionnaires on Costs Associated with Psychiatric Illness.

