##### Frequency of reported behavioral problems

The 24 items of the Revised Memory and Behavioral Problem Checklist (RMBPC)
[25] are used to make an inventory of the number of problems family caregivers encounter. Respondents have to rate from 0 to 4 the frequency of the occurrence of the specific behavior (0 = never; 1 = seldom; 2 = regularly; 3 = often; 4 = always). The total number of behaviors problems (0 – 24) will be calculated as well as the total mean score (Behavior Frequency Score). The Behavior Frequency can be subdivided into scores on Depression (9 items), Disruptive behavior (8 items) and Memory-related problems (7 items).

Other variables that may act as confounders or modifying variables will be measured. This concerns the following demographic characteristics of caregivers: sex, age, relationship (spouse, child or other), level of education and living arrangement (living together with care recipient). Relevant patients characteristics are: sex, age, duration of symptoms (as perceived by caregiver), functional status (assessed by means of a Dutch translation of a short version of the IQCODE
[29]) and living condition (independently or within care facility).

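### The between-arm analysis does not commit to adjusting for intake CES-D or the two stratification factors, and so forgoes precision that is already paid for

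*Protocol article*

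**What the plan says.** The Statistical analysis section tests differences between the arms with paired t-tests and effect sizes, and then adds: "By using multiple regression analyses, we can correct for possible confounders". It names no covariate and no measurement time for that regression.

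The Randomization section fixes the strata: "Before randomization participants are stratified on the basis of two factors (sex: male/female and relationship: spouse/other". Randomisation follows assessment.

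Table 1 (Outcome measures in the RCT) has a block headed "Confounders/Modifying variables". It holds the Mastery Scale, the SSCQ, RMBPC behaviour problems, demographic variables, diagnosis/duration and the IQCODE. CES-D is not in the block. It stands among the outcomes, with a value at Intake and none at T=1, so the intake score is the only baseline value. Mastery, SSCQ and RMBPC frequency are taken at T=1 and again at T=3, T=4 and T=5.

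Sex and relationship appear under Frequency of reported behavioral problems, introduced by: "Other variables that may act as confounders or modifying variables will be measured". Relationship is coded there in three levels (spouse, child or other), whereas the randomisation uses two.

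The sample size assumes no covariate: "Assuming an alpha of 0.05 and a statistical power (1-Beta) of 0.80 in a two-tailed test, we need 63 respondents in each of the conditions", with "A standardized effect size (Cohen's *d*) of 0.50 is considered a relevant treatment effect".

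**The concern.** In a randomised trial, covariates are adjusted for mainly to gain precision and to respect the design. The baseline value of the outcome usually gains the most. The stratification factors belong in the model because the allocation was balanced on them. The article describes its regression as a correction for possible confounding, and neither kind of covariate has an assured place in it.

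This regression carries more weight than usual. A paired t-test, taken literally, compares measurements within persons and not two independent arms. That is a separate question, but it leaves the regression as the natural between-arm model for the post-test.

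There is also a smaller, conditional matter. Three scales in the confounder/modifier block are measured after randomisation as well as before it, and they reflect things a coping course may change. If their T=3 values entered the model as covariates, part of the treatment effect would be adjusted away.

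**Working it through.** **Inputs from the article (Sample size):** d = 0.50 (SD set to 1), two-sided alpha 0.05, power 0.80, 63 per arm; "Overall, we need 126 respondents to complete the study in total"; at least 25% dropout and 175 recruited.

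**Assumed, because the article gives no figure:** correlation r between intake and T=3 CES-D, 0.3 to 0.7; share of CES-D variance explained by the strata, 2% to 10%.

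**1. The plan's own figure.** n per arm = 2(1.960 + 0.842)² / 0.50² = 62.8, rounded up to 63. Power at 63 is Φ(0.50/√(2/63) − 1.960) = Φ(2.806 − 1.960) = 0.801. The noncentral t gives 0.795 at 63 and 0.801 at 64. The figure reproduces, without adjustment. Dropout is covered: 126/0.75 = 168, and 175 × 0.75 = 131.

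**2. Adding intake CES-D.** The residual SD becomes √(1 − r²), so power = Φ(2.806/√(1 − r²) − 1.960). For a comparison of change scores the SD is √(2(1 − r)).

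| r (assumed) | Post-test only, n = 63 | Change score, n = 63 | Adjusted for intake CES-D, n = 63 | n per arm for 80%, adjusted |
|---|---|---|---|---|
| 0.3 | 0.801 | 0.660 | 0.837 | 58 |
| 0.4 | 0.801 | 0.726 | 0.865 | 53 |
| 0.5 | 0.801 | 0.801 | 0.900 | 48 |
| 0.6 | 0.801 | 0.881 | 0.939 | 41 |
| 0.7 | 0.801 | 0.952 | 0.976 | 33 |

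Against the unadjusted post-test comparison, the gain runs from 0.837 − 0.801 = 0.04 to 0.976 − 0.801 = 0.17. Against a change-score comparison it is smaller when r exceeds 0.5 (0.06 at r = 0.6, 0.02 at r = 0.7). It is the same at r = 0.5 and larger below that.

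**3. Adding the strata.** With residual SD √(1 − R²), power at 63 per arm is 0.809, 0.821 and 0.841 for R² of 2%, 5% and 10%, a gain of 1 to 4 points. If the strata are balanced by design but ignored in the test, the actual two-sided alpha is about 2(1 − Φ(1.960/√(1 − R²))) = 0.048, 0.044 and 0.039. The test is slightly conservative and the estimate is not biased.

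**4. The conditional risk.** Suppose a T=3 scale were used as a covariate, the course moved it by a SDs, and its within-arm correlation with CES-D were ρ. The adjusted effect would be 0.50 − aρ. With a from 0.2 to 0.5 and ρ from 0.3 to 0.6 (assumed), this runs from 0.50 − 0.06 = 0.44 to 0.50 − 0.30 = 0.20, that is, 12% to 60% of the effect removed. This applies only if post-randomisation values are used, which the article does not say.

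**The case against.** The strongest reply is that this is a condensed article and that the exact covariate set belongs in an analysis plan that is not shown. The regression sentence cites no list. Table 1 is a schedule of instruments, and CES-D would not normally be listed a second time as a confounder when it is the primary outcome. Intake CES-D is therefore unnamed, not excluded, and sex and relationship are named candidates. All of this stands, and it limits the point to one of commitment. It does not remove the point, because the article does describe its adjusted analysis, and describes it in terms that assure a place to neither the baseline outcome nor the design factors.

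A second reply is that paired tests suggest pre-post data, so that baseline would be used in some form. If change scores were compared between the arms, the gain from adjustment would indeed be smaller for r above 0.5. The article does not say that they will be.

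Three stronger readings are tempting and are not supported:

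- A reader might infer from Table 1 that post-randomisation mastery, SSCQ or RMBPC values will be adjusted for, biasing the effect towards zero. The crosses at T=3 to T=5 show when the questionnaires are given, not which values enter a model. T=1 values exist, and since randomisation follows assessment they can be read as pre-randomisation.
- A reader might infer that the trial is underpowered. For a two-sample comparison of post-test scores it is not, because the 63 per arm never relied on adjustment. Only a change-score comparison with r below 0.5 would fall under 80%, and the article specifies neither.
- A reader might apply the 31% dropout quoted in the Discussion to the 175 recruited, leaving about 60 per arm. That figure is an average from a review of dropout from internet-based treatment. The planning assumption for data collection is at least 25%.

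**Conclusion.** The point holds as a modest and inexpensive improvement. The article does not commit to adjusting the primary comparison for intake CES-D or for the stratification factors. Under assumed correlations of 0.3 to 0.7, this forgoes about 4 to 17 points of power against an unadjusted post-test comparison at 63 per arm and d = 0.50. The strata account for perhaps 1 to 4 further points under assumed variance shares of 2% to 10%, each effect being reckoned on its own. No shortfall against the planned 80% is shown and no bias is planned. The possible use of post-randomisation covariates is a risk to close by wording, not an error in the text.

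**What to change.** Name one primary model: T=3 CES-D regressed on arm, intake CES-D, sex and relationship, with relationship coded spouse/other as in the randomisation. Label adjustment for any other covariate as a sensitivity analysis. Add a sentence that only values measured before randomisation (Intake or T=1) of mastery, SSCQ and RMBPC frequency may be used as covariates or modifiers; their later values can be analysed as outcomes or mediators. If an analysis plan exists and already says this, a cross-reference is enough. Every variable is already collected, so the cost is a few lines of text, and neither the sample size nor the assessment schedule changes.
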